## Abstract

**Introduction:**

Severe osteogenesis imperfecta (OI) is a debilitating disease with no cure or sufficiently effective treatment. Mesenchymal stem cells (MSCs) have good safety profile, show promising effects and can form bone. The Boost Brittle Bones Before Birth (BOOSTB4) trial evaluates administration of allogeneic expanded human first trimester fetal liver MSCs (BOOST cells) for OI type 3 or severe type 4.

**Methods and analysis:**

BOOSTB4 is an exploratory, open-label, multiple dose, phase I/II clinical trial evaluating safety and efficacy of postnatal (n=15) or prenatal and postnatal (n=3, originally n=15) administration of BOOST cells for the treatment of severe OI compared with a combination of historical (1–5/subject) and untreated prospective controls (≤30). Infants<18 months of age (originally<12 months) and singleton pregnant women whose fetus has severe OI with confirmed glycine substitution in *COL1A1* or *COL1A2* can be included in the trial.

Each subject receives four intravenous doses of 3×10^6^/kg BOOST cells at 4 month intervals, with 48 (doses 1–2) or 24 (doses 3–4) hours in-patient follow-up, primary follow-up at 6 and 12 months after the last dose and long-term follow-up yearly until 10 years after the first dose. Prenatal subjects receive the first dose via ultrasound-guided injection into the umbilical vein within the fetal liver (16+0 to 35+6 weeks), and three doses postnatally.

The primary outcome measures are safety and tolerability of repeated BOOST cell administration. The secondary outcome measures are number of fractures from baseline to primary and long-term follow-up, growth, change in bone mineral density, clinical OI status and biochemical bone turnover.

**Ethics and dissemination:**

The trial is approved by Competent Authorities in Sweden, the UK and the Netherlands (postnatal only). Results from the trial will be disseminated via CTIS, ClinicalTrials.gov and in scientific open-access scientific journals.

**Trial registration numbers:**

EudraCT 2015-003699-60, EUCT: 2023-504593-38-00, NCT03706482.

Strengths and limitations of this studyThis is a protocol for an open-label clinical trial; which means that there is no randomisation and the treatment is known both to the families and the trial personnel.Osteogenesis imperfecta is by nature a heterogeneous and variable disease, which may impact the possibility to satisfactorily evaluate the effect of treatments. To address this and collect reliable data, the Boost Brittle Bones Before Birth (BOOSTB4) trial collects data longitudinally and includes multiple follow-up assessments of each subject.The trial may be underpowered to show improvements in efficacy. Therefore, if the trial yields a positive result, a larger subsequent multicentre pivotal trial may be needed.

## Introduction

Osteogenesis imperfecta (OI) is a rare clinically and genetically heterogeneous group of heritable disorders of connective tissue characterised by osteopenia, growth restriction, bone deformities, fractures and chronic pain.^1^ Originally, OI was classified into four types according to clinical, radiological and histological findings, where type 1 refers to the mildest form, type 2 to the perinatally lethal form, type 3 to the most severe form compatible with life and type 4 to an intermediate group with moderate to severe types of OI.^2^ This classification covers 85%–90% of persons with OI and includes >1500 different autosomal dominant sequence variations in the genes coding for type I collagen (*COL1A1* or *COL1A2*).^1–3^ There is currently no curative treatment for OI, with the only available pharmaceutical treatments failing to address the underlying molecular pathology, the collagen defect.^4^ Treatment is aimed at increasing overall bone strength to prevent fractures and maintain mobility. Bisphosphonates are used to reduce bone resorption and increase bone mass.^5^ However, two meta-analyses of randomised trials on bisphosphonate treatment for OI did not demonstrate improvement in fracture rates, reduction of pain or improved functional mobility, although multiple studies report this independently.^6 7^

One child among 10–20 000 is born with OI. Diagnosis of severe types of OI is often made at the routine fetal anomaly ultrasound scan mid-pregnancy, or earlier if first trimester scanning is routine. Early treatment of OI is preferred to minimise irreversible pathology. Prenatal intervention offers multiple potential advantages over postnatal approaches; ameliorating and preventing damage that has begun already during fetal life, the relatively naive fetal immune system may permit the development of immune tolerance towards donor cells, infusion into the systemic fetal circulation may avoid sequestration of the cells in the lungs because circulatory shunts allow the pulmonary circulation to be bypassed, fetal life is a time of natural stem cell proliferation and migration to different anatomic compartments. Also, prenatal administration may enhance the effect of mesenchymal stem cells (MSCs) because there will be a lesser amount of poor quality OI type collagen that requires replacement, and finally, the possible psychological benefits for parents of commencing treatment as early in the child’s life.^8^

The investigational medicinal product (IMP) investigated in the BOOSTB4 trial is an advanced therapy medicinal product consisting of allogeneic ex vivo expanded human fetal liver-derived MSCs from the first trimester of pregnancy. MSCs are multipotent stem cells and are promising candidates in regenerative medicine due to their low immunogenic profile that allows the possibility of performing cell transplantation across major histocompatibility barriers without immunosuppression.^9 10^ In addition, they have the potential to differentiate along the osteogenic, chondrogenic and adipogenic lineages and have a good safety profile with minimal oncogenic risk.^11–16^ Two meta-analyses of eight and 55 randomised controlled trials investigating intravascular administration of naïve MSCs to 321 and 2696 subjects, respectively, did not detect an association between non-fever acute infusional toxicity, organ system complications, thrombotic/embolic events, infection, death or malignancy.^17 18^ The only significant association with intravascular administration of MSCs was a transient fever.^17 18^ The first clinical infusion of MSCs was performed over 20 years ago and adult MSCs have since been used in a diverse range of conditions in thousands of patients.^9 17^ Studies show that MSCs derived from developmentally younger donor sources present characteristics suggesting a stronger cell therapeutic potential than adult MSCs, and this knowledge is being translated into clinical application. First trimester fetal MSCs are found at a higher frequency, are less mature on the transcriptomic level, have a greater colony-forming and proliferation capacity and are more immune modulatory compared with adult MSCs.^10 19–22^ Interestingly, fetal MSCs differentiate into more lineages than MSCs derived from adult tissues, like skeletal muscle, oligodendrocytes and hepatic cells^23–25^ and differentiate more readily into bone than adult MSCs. In a direct comparison of fetal MSCs and MSC derived from Wharton’s Jelly, adult bone marrow and adipose tissue, fetal MSCs had higher levels of osteogenic genes under basal conditions.^26 27^ On osteogenic differentiation, fetal MSCs produced more robust osteogenic gene expression, induced more calcium deposition in vitro and reached higher levels of osteogenic gene upregulation in vitro and in vivo.^26–28^ First trimester fetal liver MSC were selected for use in this trial given their superior osteogenic differentiation capacity, their safety profile and the feasibility of manufacturing a high-quality Good Manufacturing Practice (GMP)-compliant off-the-shelf product with retained efficacy.

Donor cell engraftment in bones has been reported to be between 0% and 16.4% after stem cell transplantation in both human cases of OI and mouse models.^29–34 37 38^ It is difficult to determine if such low levels of engraftment could result in adequate synthesis of healthy type I collagen and significant clinical improvement. However, Panaroni *et al* reported that in utero transplantation of healthy bone marrow to the Brtl OI mouse resulted in donor cell engraftment of 1%‒2% in the bones, which in turn resulted in a 20% production of healthy collagen in the host bones.^30^ The transplantation eliminated the perinatal lethality of Brtl mice, and furthermore the femora of treated Brtl mice had significant improvement in geometric parameters compared with Brtl mice and in mechanical properties compared with wild-type mice. Hence, low level engraftment of cells producing healthy collagen may lead to significant improvements in bone development.

Transplantation of MSCs is not a cure, but it is currently the only therapy available in clinical phase trials for OI that may result in healthy bone cells and production of healthy collagen. Other treatments developed for OI are based on modifying the action of the patient’s own cells, and hence can only result in increased quantity of bone rather than improved quality of bone. However, the clinical effects of MSC administration may not be persistent and therefore redosing may be required. The interval for re-dosing is currently not known.

There is increasing interest in treatment with MSCs and a growing number of requests from patients and their physicians to provide it. In the absence of a clinical trial, prenatal and postnatal MSC transplantation for OI is likely to be practised around the world on a case-by-case basis, making it impossible to evaluate any effects that the intervention might have. Considering the complexity of this field and the distribution of cases, an international trial is the only realistic and ethically correct approach to enable accurate evaluation of the intervention. BOOSTB4 is the first clinical trial that will assess whether postnatal or prenatal and postnatal repeated intravenous administration of MSCs is a safe and potentially effective treatment option for severe OI. The BOOSTB4 trial will also provide a well-defined framework for assessment of children and fetuses with OI treated with fetal MSCs.

## Methods and analysis

### Trial design

Boost Brittle Bones Before Birth (BOOSTB4) is an exploratory, open-label, multicentre, phase I/II trial evaluating safety and efficacy of four postnatal intravenous doses (n=15 infants) or one prenatal and three postnatal intravenous doses (n=3 fetuses in the amended protocol, in the original protocol it was n=15 fetuses) of allogeneic expanded fetal MSCs (BOOST cells) for the treatment of severe OI compared with a combination of historical (1–5/subject) and up to 30 untreated prospective controls. Please see the trial synopsis in online supplemental material.

10.1136/bmjopen-2023-079767.supp1Supplementary data

### Setting

The Sponsor for this academic trial is Karolinska Institutet (coordinator) in Sweden. The trial sites are five maternity/fetal medicine and paediatric institutions; Karolinska University Hospital in Sweden (coordinating trial centre, OI and maternal/fetal medicine and manufacturer of the IMP), University College London (trial centre, maternal/fetal medicine) and Great Ormond Street Hospital for Children (trial centre, OI) in the UK and Leiden University Medical Centre (trial centre, maternal/fetal medicine) and University Medical Centre Utrecht (trial centre, OI) in the Netherlands.

### Investigational medicinal product

The IMP BOOST cells consists of cryopreserved expanded allogenic human first trimester liver-derived MSCs (the liver is the blood-forming organ at this time of development) obtained from early elective surgical terminations of pregnancy (see the Ethics and Dissemination section for information on donor information and consent). The IMP is manufactured under GMP, and the cells are isolated, expanded up to passage four and then cryopreserved as an off-the-shelf product ready to be thawed and reconstituted prior to administration. The cells are tested according to the Product Specification for sterility, endotoxin and mycoplasma with methods conforming to Pharmacopoeia, and they are further tested for expression of MSC markers by flow cytometry and for efficacy by a bone differentiation assay. The Mechanism of Action of the IMP is engraftment and bone differentiation. Two donors are used in the BOOSTB4 trial. At least 80 clinical doses of MSCs, and MSCs for retention samples and all safety and functionality analyses, will be manufactured from two donors.

### Eligibility and recruitment

The inclusion and exclusion criteria for the three trial groups are described in table 1. The upper age limit was amended from maximum 12 months of age to 18 months of age in the postnatal group. This change to the original protocol has been approved by the Competent Authorities, and was implemented to allow for inclusion of more subjects to the postnatal group. All subjects (the postnatal, prenatal and control groups) will receive bisphosphonate treatment. At least one dose of bisphosphonate must be administered before the first dose of stem cells in the postnatal group. In the prenatal group, the first dose of bisphosphonates will be administered after birth. Acceptable types of concomitant medication including bisphosphates during the trial and until the 12 month follow-up are pamidronate (preferred) or neridronate, and the annual dose of bisphosphate is 8‒12 mg/kg body weight per year.

**Table 1 T1:** Inclusion and exclusion criteria for subjects in the BOOSTB4 trial

Inclusion criteria		
**Postnatal group (n=15**)*†	**Prenatal group (n=3**)*‡§	**Control group (n=18–120**)*
Parent’s/legal guardian’s signed informed-consent form Clinical diagnosis of OI type 3 or severe 4 *AND* Molecular diagnosis of OI (glycine substitution in the collagen triple-helix encoding region of either the *COL1A1* or *COL1A2* gene) Age less than 18 months¶ (calculated from gestational week 40+0, ie, the corrected age) Parent/legal guardian over 18 years of age	Woman has signed the patient consent form Only women where termination of the pregnancy is no longer possible or where the women are committed to continue the pregnancy may be included in the trial Suspicion of OI type 3 or severe 4 in the fetus on ultrasound findings *AND* Molecular diagnosis of OI in the fetus (glycine substitution in the collagen triple-helix encoding region of either the *COL1A1* or *COL1A2* gene) Gestation age between 16+0 and 35+6 weeks+days Pregnant women over 18 years of age	*Matched historical controls (1-5/subject):* Parent’s/legal guardian’s signed informed-consent form Clinical and molecular diagnosis of OI (glycine substitution in the collagen triple-helix encoding region of either the *COL1A1* or *COL1A2* gene) Data on fractures and growth are available Parent/legal guardian over 18 years of age *Prospective untreated controls (n=up to 30):* Postnatal participation: the inclusion criteria for the postnatal group apply Prenatal participation: the inclusion criteria for the prenatal group apply, except inclusion criteria 2

Exclusion criteria		
Postnatal group (n=15)	Prenatal group (n=3)§	Control group (n=18–120)
Existence of other known disorder that might interfere with the treatment, such as, but not limited to organ disfunction (eg, liver or renal failure or bronchopulmonary dysplasia), congenital heart defect, hypoxic encephalopathy l–lll, severe neurological problems, immune deficiencies, muscle diseases, severe malformations or syndromes diagnosed by clinical examination Any contraindication for invasive procedures such as a moderate/severe bleeding tendency Known risk factors for clotting, such as, but not limited to previous blood clot, family history of clots, clotting disorder (inherited or acquired), heart failure, inflammatory disorders (eg, lupus, rheumatoid arthritis, inflammatory bowel disease) Positive Donor Specific Antibody-test Known allergy/hypersensitivity to Fungizone and/or Gensumycin Abnormal karyotype or other confirmed genetic syndromes Oncologic disease (previous or current malignancy) Inability to comply with the trial protocol and follow-up schedule Inability to understand the information and to provide informed consent	Multiple pregnancy Coexistence of other disorder that might interfere with the treatment, as judged by the Investigator or the patient’s obstetrician Abnormal fetal karyotype or other confirmed genetic syndrome Any contraindication for invasive procedures such as a bleeding tendency or contagious infections, such as, but not limited to HIV, syphilis, hepatitis B, hepatitis C or other known infectious diseases that can harm the fetus Known risk factors for clotting, such as, but not limited to previous blood clot, family history of clots, clotting disorder (inherited or acquired), heart failure, inflammatory disorders (eg, lupus, rheumatoid arthritis, inflammatory bowel disease) Positive Donor Specific Antibody-test Known allergy/hypersensitivity to Fungizone and/or Gensumycin Oncologic disease in woman or fetus (previous or current malignancy) Unwilling to or cannot undergo delivery by Caesarean section Inability to comply with the trial protocol and follow-up schedule Inability to understand the information and to provide informed consent	*Matched historical controls (1-5/subject):* Existence of other disorder that might interfere with the trial. No lung hypoplasia (type 2 OI) Abnormal karyotype *Prospective untreated controls (n=up to 30):* Postnatal participation: the exclusion criteria, except exclusion criterium 2, 3, 4 and 5 (contraindication for invasive procedure, known risk factor for clotting, Positive Donor Specific Antibody-test and Known allergy/hypersensitivity to Fungizone and/or Gensumycin) for the postnatal group apply Prenatal participation: the exclusion criteria, except exclusion criterium 1, 4, 5, 6 and 7 (multiple pregnancy, contraindication for invasive procedure, known risk factor for clotting, Positive Donor Specific Antibody-test and Known allergy/hypersensitivity to Fungizone and/or Gensumycin) for the prenatal group apply

For inclusion, all criteria should apply. For exclusion, one is enough to exclude.

Prenatal group: after birth and before the second dose, subjects in the prenatal group will be assessed for the inclusion and exclusion criteria for the postnatal group.

*All subjects (the postnatal, prenatal and control groups) will receive bisphosphonate treatment.

†At least one dose of bisphosphonate must be administered before the first dose of stem cells.

‡The first dose of bisphosphonates will be administered after birth.

§In the original trial protocol, the prenatal group was n=15. This amendment has been approved by the Competent Authorities.

¶In the original trial protocol, it was ‘Age less than 12 months’. This amendment has been approved by the Competent Authorities.

BOOSTB4, Boost Brittle Bones Before Birth; OI, osteogenesis imperfecta.

Information about the BOOSTB4 trial has been distributed to specialist OI services and fetal medicine units in Europe, and the BOOSTB4 trial team can also be contacted directly by families or physicians via email or the trial specific website (www.boostb4.eu) where the Patient Information Leaflet is available in several languages. The potential subjects are invited to visit the trial site or have an organised video meeting and provide their oral and written consent to be screened for participation. At least 3 days will be required for the parents/legal guardians to consider participation in the trial. For all children enrolled in the trial, a signed informed-consent form for the main trial is required from the mother and the father, if she/he has parental responsibility (see online supplemental material for the screening and main trial participation consent forms for the postnatal and prenatal groups, and www.boostb4.eu for the Participant information sheets). For prenatal inclusion, only the pregnant woman needs to sign the informed-consent form, but both parents are encouraged to sign. After the birth of a child in the prenatal group, the inclusion and exclusion criteria for the postnatal group must be fulfilled (table 1), and both parents must reconsent their participation in the trial before the first postnatal dose. Consent may be withdrawn at any time without a reason being stated. The Sponsor will hold clinical trial insurance that covers all enrolled subjects receiving active treatment.

10.1136/bmjopen-2023-079767.supp2Supplementary data

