### Blinding, intervention and follow-up

It would not be ethically appropriate to perform a randomised double-blind placebo-control trial in this population, particularly regarding the risks of the prenatal infusion procedure and the vulnerability of the subjects. No blinding or randomisation will therefore take place.

Four intravenous doses of BOOST cells are administered at 4 month intervals (range 3–5 months), please see figure 1 for an overview of the trial. For postnatal subjects, the first dose must be administered before 18 months of age (in the original protocol, it was before 12 months of age; an amendment that has been approved by the Competent Authorities). For prenatal subjects, the first dose will be given in utero during gestational weeks+days 16+0–35+6 via ultrasound-guided injection into the umbilical vein within the fetal liver, and the final three doses are administered postnatally. Each dose contains 3×10^6^ allogeneic expanded human fetal liver MSCs per kg bodyweight. All doses to a subject will be derived from one donor. No preconditioning or medicines after the administration will be administered.

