One to five historical controls per subject and up to 30 prospective controls in total will be included and matched to each subject.

*No mixed OI types (eg, OI type 3/4, is allowed).

†Clinical diagnosis, molecular diagnosis not required at this time point.

OI, osteogenesis imperfecta.

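### Historical controls need a genetic diagnosis but with no date for it, so a control's entry can depend on surviving and being tested after the compared follow-up has started

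*Protocol article*

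**What the plan says.** Table 1 (Eligibility and recruitment) makes the glycine substitution an entry condition for every group, but only some groups have it tied to a time.

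- Postnatal subjects: "Molecular diagnosis of OI (glycine substitution in the collagen triple-helix encoding region of either the" two collagen genes, together with "Age less than 18 months". The section Blinding, intervention and follow-up adds that "the first dose must be administered before 18 months of age". The result therefore precedes the first dose.
- Prenatal subjects: "Molecular diagnosis of OI in the fetus", so it precedes the dose given in utero.
- Prospective controls: they take over the molecular criterion of the corresponding treated group.
- Historical controls: "Clinical and molecular diagnosis of OI (glycine substitution in the collagen triple-helix encoding region" of either gene, and "Data on fractures and growth are available". There is no age limit, no test date and no index date.

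Table 2 matches controls on OI type and on age at start of bisphosphonates (first 2 months, or 2 to 12 months). Time of OI diagnosis is an extra matching factor, used only when more than five controls are found. Its footnote reads "Clinical diagnosis, molecular diagnosis not required at this time point". Historical data come from routine national follow-up. The key secondary endpoint counts fractures from baseline to 12 months after the last dose, and to 10 years after the first.

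**The concern.** A treated child is known to carry the variant when its follow-up starts. A historical control may acquire that status during or after the period being compared. For such a control, the time between the index age (the matched subject's age at first dose) and the test is included only because the child lived, remained in care and was eventually tested. A similar child who died or was lost to care before testing never becomes a control.

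Aligning the ages of subject and control does not remove this, because eligibility still rests on something that happened later. What is at stake is the historical comparison of fractures and growth, and any survival figures set beside it. Historical controls may number 18–90 against at most 30 prospective ones, so they can carry most of the external comparison.

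**Working it through.** **1. Control numbers.** Subjects: 15 + 3 = 18. Historical controls: 18 × 1 = 18 to 18 × 5 = 90, as stated under Statistical analysis. With prospective controls the maximum is 90 + 30 = 120, as in Table 1. Both figures reproduce.

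**2. Window.** Four doses have three intervals of 4 months (range 3–5), followed by 12 months: 3 × 4 + 12 = 24 months (21–27). A postnatal child dosed just before 18 months is about 18 + 24 = 42 months old at the end (39–45). A control tested anywhere in that window, or after it, still meets Table 1.

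**3. Does matching close the gap?** Bisphosphonate start by 12 months fixes when the disease was recognised and treated, not when the gene was tested. The diagnosis-time factor is conditional and, by its footnote, clinical only. Neither sets a latest test date.

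The article gives no test ages, death risks or fracture rates. Steps 4 to 6 therefore rest on assumed values and show only direction and range.

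**4. Selection through death.** Let *m* be the death risk over the window, *q* the share of controls tested only at its end, and *k* the fracture rate of children who die relative to survivors.

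- Observed control mortality = (1−q)m / [(1−q) + q(1−m)]. For m = 0.10 and q = 0.5 this is 0.05/0.95 = 5.3%. With q from 25% to 100%, a true 2% becomes 1.5% to 0, 10% becomes 7.7% to 0, and 20% becomes 15.8% to 0.
- Control fracture rate, seen/true = [(1−obs) + obs·k] / [(1−m) + m·k], where obs is the observed mortality. For k = 2–3 it runs from 0.995 (m = 0.02, q = 0.25, k = 2) to 1/1.4 = 0.71 (m = 0.20, q = 1, k = 3). Controls look better than they should.

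**5. Selection through severity, two classes.** Half the children fracture at twice the rate of the others (true mean 1.5) and are *r* times as likely to be tested late. The late-tested mean is (2r+1)/(r+1). For r = 1.5 and q = 0.25, seen/true = (0.75 × 1.5 + 0.25 × 1.6)/1.5 = 1.02. For r = 3 and q = 1, it is 1.75/1.5 = 1.17. Controls look worse than they should.

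**6. Selection through severity, gamma rates.** Child-specific rates have mean 1 and CV 0.5–1.0, half of the controls are tested late, and the cells are inactive. The rate ratio is treated/control, so a value below 1 makes the cells look better.

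- *(a) Treated children and the other controls taken as unselected.* If late testing is proportional to the rate, the late-tested mean is x = 1 + CV² = 1.25–2.0. If testing saturates (50–80% tested), x = 1.08–1.50. Rate ratio = 1/[1 + 0.5(x−1)] = 0.96 to 0.67.
- *(b) Treated children and the other controls selected by an early test whose hazard is proportional to the rate.* Let S₁ be the share untested at the index age (0.2–0.7), S₂ the share never tested (0–0.2), and c = CV². Early-tested mean E = (1 − S₁^(1+c))/(1 − S₁) = 1.08–1.70. Late-tested mean L = (S₁^(1+c) − S₂^(1+c))/(S₁ − S₂) = 0.20–1.01. Rate ratio = E/[0.5E + 0.5L]. The lowest value (CV 0.5, S₁ = 0.7, S₂ = 0.2) is 1.199/1.106 = 1.08. The highest (CV 1.0, S₁ = 0.2, S₂ = 0) is 1.2/0.7 = 1.71.

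Both (a) and (b) assume that more fractures make testing more likely, yet they point in opposite directions. The sign depends on whether the treated children went through the same kind of selection.

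**The case against.** **The article is condensed.** The full protocol may set a test date, and the missing rule alone would not be a finding. That limits what can be claimed: the text shows that late-tested controls can enter, not that any did. But Table 1 is printed in detail, with age limits and timing footnotes for the other groups, and the historical criterion as written is open-ended. The point concerns how that criterion is set.

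**The footnote has a narrow purpose.** It defines what makes a diagnosis prenatal or postnatal for an optional matching factor. A reader might take it as permission for tests years later. It does not say that. It shows only that the molecular result may follow the clinical diagnosis, with no limit stated.

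**The trial is exploratory and descriptive.** There is no power calculation, each subject is also compared with itself, and the article promises caution about bias. All of this stands and lowers the stakes. The promise names no rule on test timing, however.

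**Mild courses are largely excluded.** A reader might infer that mild cases drop out of the controls for want of a test. Matching on type 3 or severe type 4, and on bisphosphonate start within 12 months, covers most of that, so it is not part of the point.

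**A dated criterion does not remove all later conditions.** Historical controls also need signed parental consent and available records, both obtained afterwards. And for a prenatal subject, a strict cut-off at first dose would demand a fetal genetic result, although the footnote asks only for a prenatal clinical diagnosis. Both objections are right, and the fix is framed to allow for them.

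**Conclusion.** The point holds for the historical comparison of fractures and growth. As written, Table 1 lets a historical control qualify through a genetic result obtained after the compared follow-up began, while treated subjects and prospective controls cannot. The control fracture rate may come out too high or too low. Under the assumptions shown, inactive cells could give a rate ratio anywhere from about 0.67 to 1.71. That range illustrates possible size and is not an estimate for this trial.

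Two stronger readings are not supported. One is that late testing must make the cells look effective on fractures. That follows only if treated infants are taken as unselected, although they too needed a positive test, before inclusion. The other is that a planned mortality comparison is spoiled. The article lists mortality under the primary safety endpoint, which concerns administration-related events, and specifies no mortality comparison with historical controls. If survival is nevertheless set side by side descriptively, the controls would be favoured.

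The primary safety assessment of treated subjects, the within-subject comparisons and the prospective controls are not affected.

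**What to change.** Add to the historical-control criteria and the description of the comparison:

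1. Record the date of the genetic result for every historical control.
2. Prefer controls whose result was available at or before the matched subject's age at first dose.
3. For later-tested controls, including those matched to prenatal subjects, count fractures, growth and survival only from the date of the result, and at the same ages as the subject.
4. Report how many controls enter this way, and show the comparison without them. This is needed because delayed entry removes the time conditioned on survival but not any selection of who gets tested.
5. State as a limitation that selection through retrospective consent and data availability remains.

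The cost is one extra date per control, a short addition to the text and one further descriptive table. Some subjects will have fewer controls or less control time, though the range of one to five per subject leaves room for losses. For the three prenatal subjects, a control tested after birth would contribute nothing to the fractures-at-birth comparison. Enrolment of treated subjects is complete, but the changes need only existing records, and long-term follow-up runs to 2032.
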